### Data monitoring

The Italian Ministry of Health has the role of oversight and ultimate authority over all the activities of the study and requires the research team to write a mid-time report about the progress of the work and a final report about the conclusion of the research.

In the mid-time report, interim analyses will be performed on the rate of recruitment from each of the clinical settings involved, and on adherence of recruited participants to the treatment protocol. Baseline and demographic data will be tested for balance between dropouts and participants who will have completed the protocol, using a 1-way analysis of variance (ANOVA), w2 test, or Fisher exact test, as appropriate. Comparison between treatment groups will be carried out at the completion of the recruitment.

Any relevant changes to the study protocol which may impact on the conduct of the study, or significant administrative aspects need to be communicate to the Italian Ministry of Health in order to obtain a formal authorization. The Pediatric Ethic Committee of Tuscany Region has assumed a role comparable to a Data Monitoring Committee, requiring the research team to write yearly reports about the progress of the work and reports about any adverse events. Any important protocol modification during the trial need to be communicate to the Ethic Committee in order to obtain a written authorization to a protocol amendment. The Pediatric Ethic Committee of Tuscany Region is independent from the sponsor and from trial investigators. Further details about it and its charter can be found at http://www.meyer.it/index.php/ricerca-e-innovazione/comitato-etico.

Periodic audits of all the relevant aspects of the clinical trial management will be conducted by a team of senior researchers not directly involved in the trial [name]. Audits will be planned every 2 months as research meetings with an order of business related to the aspects of the trial that will need a critical review (see Table 3).

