Primary outcome(s)	Changes in severity level of ASD symptomatology (Time Frame: 6 months; not designated as safety issue)
Key secondary outcomes	Changes in GI symptomatology; changes in Electroencephalogram (EEG) power, coherence and asymmetry; changes in levels of serum Lipopolysaccharide, Leptin, Resistin, Tumor Necrosis Factor – α, Interleukin- 6, P Plasminogen Activator Inhibitor – 1; changes in levels of fecal calprotectin; Changes in global ASD symptomatology assessed by Childhood Autism Rating Scale, by Social Communication Questionnaire, changes in ASD symptomatology: repetitive behaviors and sensory profiles, changes in Developmental Quotient, in Adaptive Functioning, in Behavioral Profiles, and in parental stress (time frame: 3 and 6 months; not designated as safety issue).

**Table 3 Tab3:** Composition, roles, and responsibilities of the research team coordinating and conducting the trial (Steering Committee), of the Auditing Committee and of the G-BIA (Gut-Brain Interaction in Autism) group

Research leading team/Steering Committee (see title page and author section for members)	Roles and Responsibilities
• Principal Investigator (Trained research child psychiatrist)	Design and conduct of the trial, preparation of protocol and revisions preparation of investigators brochure (IB) and CRFs [case report forms], organizing steering committee meetings, recruitment coordination, clinical assessment coordination, EEG recording coordination, intervention coordination, adverse events monitoring, data collection and entry coordination, providing of annual and final reports to the ethics committee and mid-time and final report to the Italian Ministry of Health, publication of study reports.
• Sub-Investigator (Trained research pharmaceutical chemical doctor)	Design and conduct of the trial, preparation of protocol and revisions, preparation of IB and CRFs, biochemical samples collection and analysis, biochemical measurement coordination, data collection and entry coordination, contacts with the company supplying probiotic and matched placebo and performing randomization and intervention assignment, coordination of statistical analysis, providing of annual and final reports to the ethics committee and mid-time and final report to the Italian Ministry of Health, publication of study reports.
• Trained research Biomedical Engineer	EEG data processing, EEG statistical analysis Contribution to the development of the study design

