### Final assessment

After 6 months (Time 2 - T2) from the enrollment i.e. at the end of the intervention, each subject will undergo a final assessment through the same clinical, biochemical and neurophysiological evaluations performed at T0 in order to establish the after-treatment modifications of all the primary and secondary outcome measures.

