### Assignment of interventions

After inclusion in the study and baseline assessment, participants will be assigned to the GI group or to the NGI group depending on their baseline scores at the GI Severity Index [60], as previously described. Then, participants of these two groups will blind receive a treatment with probiotics or with placebo according to a computer generating randomization sequence previously determined by the company supplying probiotic and matched placebo. The allocation ratio of intended numbers of participants will be 1:1 both in the GI and in the NGI comparison groups so that the number of children receiving probiotics or placebo will be identical respectively in the two GI and in the two NGI groups.

Randomization will be made in blocks with random sequences of independent block both in the GI and in the NGI groups; the order of interventions will be vary randomly within each block, so that the assignment blocking schedules will be unpredictable. The study will be double blind till its conclusion, so that subjects, caregivers, all research investigators and all the outcomes assessors will be blinded to treatment group assignment of all subjects till the end of data collection and analysis.

The packages containing probiotics will be indistinguishable from those containing placebo and will be enumerated progressively in the two clinical subgroups (GI: from 1 to 50; NGI from 1 to 50). The allocation sequence will be concealed and the matching between the randomization number and the contents of each package (probiotics or placebo) will be written in sealed envelopes (one for each recruited subject/randomization number) stored at the Institute of Clinical Physiology National Research Council (Pisa, Italy).

The research investigators will assign a number of treatment to each of the recruited children on the basis of their respective progressive order of enrollment inside each of the two subgroups. So, the first child enrolled in the GI subgroup will receive the treatment packages labelled “GI1”, the second child enrolled in the GI subgroup will receive the treatment packages labelled “GI2”, the first child enrolled in the NGI subgroup will receive the treatment packages labelled “NGI1” and so on.

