#### Data and statistical analysis

All data were will be collected and analyzed independently of the investigators, who will not have access to the data or to its analysis until the latter had been completed. Baseline and demographic data will be tested for balance between treatments using a 1-way analysis of variance (ANOVA), w2 test, or Fisher exact test, as appropriate. As designed by the protocol, the primary comparison for efficacy will be the responder rate according to ADOS 2 score; the analysis will be carried out on the intent-to-treat population, defined as all randomized patients who received at least one dose of study medication. Dropouts will be considered as no responders. Comparison between treatment groups will be carried out by Cochran/Mantel/Haenszel test for responder counts, controlled for basal value, on either the total population of enrolled patients and on the subset of patients completing the treatment. Post hoc-trend analysis of responders within each group will be carried out by the Cochran-Armitage trend test. All data will be analyzed by means of SAS 8.2 Stat Procedures.

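### The treatment groups are to be compared when recruitment ends, but the last-enrolled children reach the 6-month primary assessment only later, and the blinding rules run past that point

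*Protocol article*

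**What the plan says.** The Data monitoring section describes a mid-time report in which "interim analyses will be performed on the rate of recruitment from each of the clinical settings involved, and on adherence of recruited participants". The report also holds a baseline comparison of dropouts and completers. The paragraph ends: "Comparison between treatment groups will be carried out at the completion of the recruitment".

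Four other parts of the article bear on that date.

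- **Primary outcome.** Table 2 (registration data) gives it as "Changes in severity level of ASD symptomatology (Time Frame: 6 months; not designated as safety issue"). Under Data and statistical analysis, "the primary comparison for efficacy will be the responder rate according to ADOS 2 score". Table 1 schedules ADOS-2 at baseline and at 6 months, with nothing at 3 months.
- **Final visit.** The Final assessment section places it "After 6 months (Time 2 - T2) from the enrollment i.e. at the end of the intervention", and its purpose is "in order to establish the after-treatment modifications of all the primary and secondary outcome measures".
- **Blinding.** Under Assignment of interventions, subjects, caregivers, all investigators and all assessors "will be blinded to treatment group assignment of all subjects till the end of data collection and analysis". Data management and confidentiality gives the two lead investigators and the sponsor the full dataset and the treatment codes at the end of the study.
- **Access to results.** Data and statistical analysis has the data analysed independently of the investigators, who are kept from the data and the analysis until the analysis is complete. Table 3 gives coordination of the statistical analysis to the Sub-Investigator.

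**The concern.** The end of recruitment and the end of follow-up are 6 months apart for the last child. If the comparison is run on the stated date, every child enrolled in the preceding 6 months belongs to the intent-to-treat population but has no T2 rating. The primary test would then use only the earlier enrolees, with fewer children than the sample size calculation requires.

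The date also falls before the point at which the article allows blinding to end. The bar on investigators lifts when the analysis is complete, so an analysis completed at the end of recruitment could open group results to them while T2 ADOS-2 ratings are still being made. ADOS-2 is rated by clinicians and is the primary outcome, so this risk should not be left to wording.

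**Working it through.** **Step 1. The dates.** T2 is enrolment plus 6 months. The last T2 is therefore last enrolment plus 6 months, while the stated comparison is at last enrolment. The gap is 6 months whatever the accrual rate, and this needs no assumption.

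**Step 2. Which comparison is meant.** The article uses the same opening words for the efficacy test: "Comparison between treatment groups will be carried out by Cochran/Mantel/Haenszel test for responder counts, controlled for basal value". The sentence just before the disputed one compares dropouts with completers, not treatment groups. The efficacy comparison is the natural reading.

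**Step 3. Reproduce the article's sample size.** Inputs from Sample size/power: 62% and 90% response, one-sided 0.05, power 90%. With d = 0.28 and mean proportion 0.76, and no continuity correction:

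- n = [1.645·√(2·0.76·0.24) + 1.282·√(0.62·0.38 + 0.90·0.10)]² / 0.28²
- n = [1.645·0.604 + 1.282·0.571]² / 0.0784 = 37.9, so 38 per treatment.

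The article's 38 is reproduced, and power at 38 is 90.0%.

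**Step 4. Children with T2 at the end of recruitment.** The article gives a recruitment start (November 2015) and a study completion date (November 2017), 24 months apart, but no date for the end of recruitment. If completion means the last T2, recruitment can run for at most 24 − 6 = 18 months. I assume uniform accrual over A months and take A from 9 to 18. The share with T2 is f = (A − 6)/A. The number per treatment is 50f, with 50 on probiotic and 50 on placebo pooled over the GI and NGI groups.

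**Step 5. Power at that point, with no dropout.** Power = Φ{[0.28·√n − 1.645·0.604] / 0.571}.

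**Step 6. Type I error if a second, unadjusted test were run at the true end.** This is 1 − Φ₂(1.645, 1.645; ρ = √f), where Φ₂ is the bivariate normal distribution function. It is a what-if, because the article plans no second test.

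| Accrual A (assumed) | Share with T2 | n per treatment | One-sided power | One-sided type I error, only if repeated |
|---|---|---|---|---|
| 9 months | 33% | 17 | 60% | 8.5% |
| 12 months | 50% | 25 | 76% | 8.0% |
| 15 months | 60% | 30 | 83% | 7.7% |
| 18 months | 67% | 33 | 86% | 7.4% |
| All at T2 | 100% | 50 | 96% | 5% (single test) |

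In every assumed case the number with T2 is below the 38 per treatment that the article needs for 90% power. The last two columns of an accrual row are alternatives. The lower power applies if the early test is the only one. The higher type I error applies if it is repeated.

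**The case against.** The sentence closes a paragraph that confines the mid-time report to recruitment, adherence and dropout. Its evident purpose is to defer the treatment comparison, and 'recruitment' may be a slip for study completion in a text with other language errors. It could also mean a baseline balance check between treatments, which can properly be done once recruitment is complete. Both readings are possible. The shared wording with the efficacy test counts against the second without settling it. Neither removes the need to correct the sentence, which states a date and does not say that only baseline data are meant.

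Three stronger readings are tempting, and the documents do not support them.

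- *An unadjusted interim efficacy look is planned.* No section describes an efficacy interim, a stopping rule or a repeated test. The inflated type I error is purely conditional.
- *Results will be revealed to assessors still rating ADOS-2.* The article has the data analysed independently of the investigators and keeps assessors blind until data collection and analysis end. An independent or coded analysis need not unblind anyone. What remains is a risk, because access opens once the analysis is complete and an investigator coordinates it.
- *Children awaiting T2 would be counted as non-responders.* That rule covers dropouts. A child whose T2 is not yet due has not dropped out. The article simply has no rule for such children, because they should not exist at the time of analysis.

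**Conclusion.** The point holds as a contradiction over timing. The stated date for the comparison falls 6 months before the last primary assessment, and before the point at which the article lets blinding end and treatment codes be released. Followed literally, it leaves the last-enrolled children without a primary outcome and risks disclosure while ratings continue.

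That much rests on the article's text alone. The size rests on an assumed accrual period and on uniform accrual: power of about 60% to 86% over 9 to 18 months, against 96% with all 50 per treatment. All these figures assume no dropout, although the 50 per treatment were set partly to absorb it, so they are upper values. The documents do not show that the type I error is inflated as planned. If the sentence is a slip, the intended analysis is unaffected but the text still needs the correction.

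**What to change.** Replace the sentence in Data monitoring with:

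> Treatment groups will be compared once, after the last randomised child has completed T2 or left the study and the database has been locked.

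This agrees with Final assessment, Assignment of interventions, and Data management and confidentiality. The mid-time report needs no change, since it is already limited to recruitment, adherence and dropout data.

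The cost is one sentence, and a comparison up to 6 months later than the text now says. The sample size, the visits and the primary test stay as they are.

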### Ethical issues and consent to participate

The study protocol (version 1- 14/07/2014) has been approved by the Pediatric Ethic Committee of Tuscany Region in July 2014 (Approval Number: 126/2014). The current version is a protocol amendment (version 2- 14/11/2014) which has been approved in December 2014. The study will be carried out in accordance with recognized ethical principles and good clinical practice for clinical trials with food supplements. It will ensure the protection of individuals as recommended in the Oviedo Convention and in the Declaration of Helsinki. The suspension of any other treatment or intervention effective and recommended by current guidelines in ASD will not be required during the experimental protocol of treatment with probiotic/placebo. All the necessary information about the study protocol, including the aims, methods, potential risks and benefits related to experimentation, and their right to refuse participation or to withdraw consent at any time will be given to parents/legal guardians of children recruited for the study through an information sheet. No evaluations or other procedures will be carried out without the prior obtaining of acceptance of all the procedures described in the information sheet and signature of consent to participate by both parents/legal guardians of the subjects. Moreover, parents/legal guardians of all the children who will be recruited in the study will be asked to give a specific and separate consent to publication of data in an anonymous way.

Parents/legal guardians will be asked to signed an additional/ancillary consent for collection of additional blood, urinary and fecal samples and for their storage at −80 °C for future studies on the gut-brain connection (i.e. metabolomic analysis or bacterial culture tests).

Patients that will be enrolled into the study will be covered for non-negligent harm associated with the protocol by an appropriate insurance.

## Discussion

This randomized controlled trial will provide new information on the clinical and neurophysiological effects of probiotic treatment in preschoolers with ASD. To our knowledge, to date only four studies explored the effects of probiotics in ASD patients [34, 54–56] and they all showed several limitations related to sample size, lack of information about the probiotic oral supplementation or concurrent medications and diet [57]. Adams and colleagues [34] compared GI flora and GI status from stool samples of 58 children with ASD and 39 healthy typical children of similar ages, and found lower levels of total SCFAs in ASD group with a greater difference in children with autism taking probiotics. In that study, GI symptoms [34] were strongly correlated with the severity of autism. However, information about the type of probiotic oral supplementation was only partially explained. Kaluzna-Czaplinska [55] administered oral supplementation of Lactobacillus acidophilus twice a day for 2 months to a group of ASD children and found significant metabolic modifications, and an improvement in the ability to carry out orders and concentration, but no other behavioral or emotional effects. Parracho et al. [54] reported in a large sample of children with ASD a significant behavioral improvement in ASD treated with Lactobacillus plantarum WCSF1 compared to ASD treated with placebo. Recently, Tomova and colleagues [56] revealed a strong positive correlation of autism severity with the severity of GI dysfunction. In that study, probiotic diet supplementation (a combination of Lactobacillus, Bifidobacter, and Streptococci, three times a day for 4 months) normalized the microflora of autistic children. However, the effects of probiotic diet supplementation on behaviors were not investigated.

One of the possible outcome of this study is the identification of a subgroup of children with ASD and GI symptoms that could represent a particular endophenotype of ASD characterized by an abnormal gut microflora. We expect that these children, after a probiotic treatment, could show changes in GI symptomatology and in related blood, urinary and fecal biomarkers through their effects in restoring the balance of intestinal microflora, and in attenuating immunological abnormalities [32, 44]. Moreover, we expect that the treatment with probiotics in individuals with ASD and GI symptoms may produce also more significant improvement in autistic symptoms, in behavioral profiles, in adaptive functioning and in cognitive and linguistic development in comparison with individuals with ASD and GI symptoms treated with placebo. As far as we know, this is the first project that aims to examine the impact of this treatment not only on clinical but also on neurophysiological patterns and so it could provide new insights into the gut-brain connection in autism. According to our knowledge, only few studies on the presence of phthalates in subjects with ASD [52, 53] has been conducted. One study of 48 children with ASD and 45 control children reported that urinary concentrations of two phthalates (5-OH-MEHP [mono-(2-ethyl-5-hydroxyhexyl) 1,2-benzenedicarboxylate] and 5-oxo-MEHP [mono-(2-ethyl-5-oxohexyl) 1,2-benzenedicarboxylate]) were significantly increased in the ASD group compared with the control group [52]. Another study reported that 50 children with ASD had decreased glucuronidation of diethylhexyl phthalate, as measured by urinary metabolites, compared with 53 age-matched controls with typical development, despite similar phthalate exposure levels [53]. Notably, glucuronidation is a significant pathway involved in the metabolism of xenobiotics and lower glucuronidation might lead to a decreased detoxification capacity for phthalates. Therefore, the current project could add new data on the relationship between the presence of phthalates, clinical features and neurophysiological patterns in ASD. The expected risks for involved subjects are minimal and related to possible side effects of treatment with probiotics, which, as a dietary supplement, provides mild, transient and not hazardous side effect for the child’s health and to possible side effects related to draw blood that can be considered mild and transient, too. Nevertheless, one of the possible study limitations is the adherence of the families to the whole protocol, since it requires two blood collections, three urinary and fecal collections and two EEG registration and, even if these procedures are not very invasive. During previous analogue researches in our Institute, several families did not accept such kind of procedures for research purposes only. Moreover, adherence of the families could be limited by the blind and randomized study design, given the possibility of not obtaining immediate positive effects for their children if assigned to the placebo groups, mostly due to the relatively long duration of the treatment protocol. Another possible limitation of this study is the lack of a control sample of typically developing children with and without GI symptoms in order to obtain a comparison of the biomarkers levels, the phthalate presence and the neurophysiological findings of ASD subjects. On the basis of the protocol results, if the presence of the hypothesized endophenotype should be confirmed, a subsequent enrollment of a control matched group of children with typical development will be taken into consideration.
